## 1. Introduction

Coronavirus (COVID-19), caused by the severe acute respiratory syndrome SARS-CoV-2, has had a serious impact on the whole world and has triggered unprecedented health, social, and economic crises [1]. Most patients infected by SARS-CoV-2 recover in no more than a month depending on the severity of their symptoms [2,3] However, it is believed that irrespective of the severity of symptoms, around 20% of people continue to show or develop multisystemic symptoms after five weeks or more following the acute infection, while 10% continue to display symptoms after twelve weeks, despite receiving negative PCR test results and developing antibodies [4].

In the absence of a clear definition, this new symptomology had been referred to interchangeably as “Long COVID” or “Post-COVID” [5,6,7]. It is in this context that the National Institute for Health and Care Excellence (NICE) states that COVID-19 symptoms can last for 4–12 weeks and that those whose symptoms continue beyond this period and with no alternative diagnosis will be considered to have “Post-COVID syndrome” [8]. In October 2021, the World Health Organisation (WHO) released an official definition of the condition, referring to it as “Post-COVID condition” [9], a condition that occurs in individuals who were previously likely to have been infected (without diagnostic test confirmation) or confirmed to have been infected with SARS-CoV-2. 

The characteristic symptoms of this new condition are confusing, unspecific, and can be ongoing or fluctuate over time [10,11]. The most prevalent symptoms include chronic fatigue, breathlessness, fever, coughing, headaches, chest pain and/or a sore throat, muscle pain, general aches and pains, palpitations, tingling, diarrhoea, rashes, myalgia, brain fog and neurological symptoms, as well as symptoms of depression and anxiety stemming from extreme fatigue and other physical symptoms, among other causes [12,13,14]. There is a higher prevalence among women than men, with the latter making up 20% of diagnoses [15].

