Cost-efficiency and cost-utility analysis are as follows. The effectiveness of the interventions will be estimated using the difference between the SF-36 score at the baseline and at the three and six-month follow-up, and the utility will be estimated using QALYs at the three and six-month follow-up. QALYs will be calculated based on these scores using the Spanish EQ-5D tariffs [120]. Along with the number and severity of the ongoing symptoms, scores will also be used as an outcome for the analysis. Cost-efficiency will be explored through the calculation of incremental cost-efficiency ratios (ICERs) for the intervention group using the TAU group as the control. ICER is defined as the ratio between incremental costs and incremental effectiveness. In the same way, cost utility will be explored through the calculation of incremental cost-utility ratios (ICURs), which are defined as the ratio between incremental costs and incremental utilities measured on QALYs. QALYs gained in each evaluation are approximated by using the area under-the-curve technique [121]. Total costs will be calculated by adding direct and indirect costs. Direct costs will be calculated by adding the costs derived from the medication and the use of health services and clinical tests. The medication costs will be calculated by determining the price per milligram during the study period according to the Vademecum during the last year of the study, including value-added tax (VAT). The total cost of drug treatment will be calculated by multiplying the price per milligram by the daily dose in milligrams and the number of days the treatment is received. Costs derived from the use of health services will be calculated considering the data from the Oblikue database [122]. Indirect costs will be calculated based on the number of days taken on sick-leave and multiplying them by the Spanish minimum daily wage during the study period 2019–2020. We assume that data will be missing at random (MAR). Only patients with both cost and relevant outcome data at three and six-month follow-up will be included in the cost-efficiency and cost-utility analyses. Notwithstanding, sensitivity analysis imputing missing three and six-month data will test the robustness of the cost-efficiency and cost-utility results. The imputations will be performed using the package “mice” [123], freely available in cran-R [118].

Variables collected, instruments, and measures are shown in Table 1. 

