#### 2.2.9. Ethical Considerations

Ethical approval was granted by the Clinical Research Ethics Committee of Aragón (PI21/139 and PI21/454). The procedures carried out for the creation of this work complied with the ethical standards of the previously mentioned committee and with the 1975 Declaration of Helsinki. All of the subjects will sign a comprehensive consent form, their data will be anonymised, and will only be used for the purposes of the study. Participants and health care professionals will be informed of the results. Patients of the TAU group will be invited to use the APP at the end of the study. The ethics committee will be notified of any protocol modifications. 

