## 3. Results

The initial development of the ReCoVery APP has been completed at the design and architecture level. The therapeutic content (videos, information, and other types of media) has been uploaded to the APP, allowing for a fully functional version. Regarding the APP’s validation, effectiveness, and cost-efficiency study, we are now completing the recruitment phase. To date, 60 patients have participated in the study, being assessed and randomized.

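### Sick leave is valued at the minimum wage of a 2019–2020 study period, but the article's own dates put the trial at about 2021 onwards

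*Protocol article*

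**What the plan says.** The cost paragraph of section 2.2.8 (Statistical Analysis) builds the cost side of the economic evaluation from three unit prices:

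- **Sick leave**, the only indirect cost named: days off work are valued by "multiplying them by the Spanish minimum daily wage during the study period 2019–2020".
- **Medication**: priced per milligram, "according to the Vademecum during the last year of the study, including value-added tax (VAT".
- **Health services**: "Costs derived from the use of health services will be calculated considering the data from the Oblikue database", with no price year in the article.

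These are then combined: "Total costs will be calculated by adding direct and indirect costs". The total feeds the cost-efficiency ratio ("ICER is defined as the ratio between incremental costs and incremental effectiveness") and, in the same way, the cost-utility ratio with QALYs in the denominator.

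The article's evidence on when the trial ran lies elsewhere. Section 2.2.9 states "Ethical approval was granted by the Clinical Research Ethics Committee of Aragón (PI21/139 and PI21/454". The Introduction reports "In October 2021, the World Health Organisation (WHO) released an official definition of the condition". Section 3 states "we are now completing the recruitment phase. To date, 60 patients have participated in the study, being assessed and randomized".

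**The concern.** The sentence on indirect costs names calendar years for the study period, and no other part of the article places any trial activity in those years. The years are an input to the analysis: they select the unit price that multiplies every sick-leave day. Cost-efficiency is part of the stated objective in the Abstract and the Introduction.

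Two things follow if an analyst applies the named years. Sick leave that occurs during follow-up is valued at a wage from before the trial. That amount is then summed with drug costs from the study's final year, so the two components do not share a price year. An analyst who instead ignores the named years is choosing a unit cost that differs from the published text, possibly with the cost data already in hand.

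**Working it through.** **Step 1: the dates side by side.**

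| Source in the article | Date marker | What it implies |
|---|---|---|
| 2.2.8, indirect costs | 2019–2020 | stated study period |
| 2.2.9, ethics references | PI21/139, PI21/454 | approval in 2021, if the prefix is a year |
| 1, Introduction | October 2021, past tense | article written after that date |
| 4, Discussion | a cited randomised trial dated 2022 | article written in 2022 or later |
| 3, Results and 2.2.3, Sample Size | 60 randomised; 78 required | 78 − 60 = 18 still to be randomised at writing |
| 2.2.7, Variables | assessments 3 and 6 months after the intervention ends | follow-up of those 18 ends more than six months after writing |

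The stated period cannot be reconciled with the rest. Enrolment falls at about 2021–2022 and follow-up ends in 2022 or later. On these dates no follow-up sick leave falls in 2019 or 2020. At most, the baseline look-back could reach into 2020, and only for someone enrolled early in 2021. This assumes that the six-month window of the service-use inventory (2.2.7) also applies to sick leave.

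**Step 2: effect on indirect costs.** The documents give no wage, number of sick-leave days or cost, so no euro figure can be computed. Let w be the 2019–2020 daily wage and w(1+g) the wage in the true follow-up years. For d days, the plan as written gives w·d and the correct value is w(1+g)·d. The understatement as a share of the correct value is

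1 − 1/(1+g) = g/(1+g).

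For assumed g:

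- 5%: 0.05/1.05 = 4.8%
- 10%: 0.10/1.10 = 9.1%
- 15%: 0.15/1.15 = 13.0%
- 20%: 0.20/1.20 = 16.7%

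**Step 3: effect on the ratios.** Write the incremental cost as ΔC = ΔD + w·Δd, where ΔD is the between-arm difference in direct cost and Δd the between-arm difference in sick-leave days. Correcting the wage changes ΔC by g·w·Δd. If Δd = 0, nothing changes.

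- *Direct and indirect differences with the same sign.* Let s be the share of ΔC due to sick leave at the old wage. The numerator is multiplied by 1 + s·g. For s from 0.25 to 0.75 and g from 5% to 20%, this runs from 1 + 0.25 × 0.05 = 1.0125 to 1 + 0.75 × 0.20 = 1.15.
- *Opposite signs.* With invented units ΔD = +100 and w·Δd = −80, ΔC is 20 at the old wage. It becomes 100 − 80 × 1.05 = 16 at g = 5% and 100 − 80 × 1.20 = 4 at g = 20%. With w·Δd = −95, ΔC is 5 at the old wage. It becomes 100 − 95 × 1.05 = 0.25 at g = 5% and 100 − 95 × 1.20 = −14 at g = 20%. The sign can change, but only when the two components nearly cancel.

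**The case against.** The best defence is that the sentence already contains the right rule. Its operative words tie the wage to the study period, and the years are a mistaken gloss, perhaps carried over from other text. An analyst who follows the rule would use the real years. This is a fair reading of the intent, and it makes the matter a dating error more than a deliberate choice of valuation. It does not remove the problem, because the sentence then contradicts itself and leaves two possible unit costs.

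Four stronger readings may tempt a reader, and the documents do not support them:

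- *That 2019–2020 is proven to lie wholly before the trial.* No recruitment start date is given. The 2021 and 2022 markers in the Introduction and Discussion date the manuscript, not the first enrolment. The start date rests mainly on reading PI21 as a year. The inference is strong, but it remains an inference.
- *That drug prices will be several years later than the wage.* The final study year is not stated. The dates support 2022 at the earliest, a gap from 2020 of at least 2022 − 2020 = 2 calendar years, and give no upper figure.
- *That the ICER and ICUR are materially distorted.* The percentages apply to total indirect costs under assumed wage growth. The ratios respond only to the between-arm difference in sick leave, which is unknown.
- *That the missing price year for services, or a missing inflation method, is a further defect.* An article commonly leaves such details to the full protocol or analysis plan.

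**Conclusion.** The point holds. The years attached to the sick-leave wage in section 2.2.8 conflict with the article's own dates, which indicate a trial running from about 2021 into 2022 or later. Applied literally, the text values follow-up sick leave at a pre-trial wage and adds it to drug costs from the study's final year.

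The size is not known. Indirect costs would be understated by g/(1+g), but every value of g used here is an assumption. The effect on the two ratios may be small. It matters most if the arms differ in sick leave and that saving nearly offsets a difference in direct cost. The SF-36 analysis and the other clinical effectiveness results are untouched. The correction should be made before the cost data are analysed, but the point does not threaten the trial's main outcome.

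**What to change.** In the indirect-cost sentence of section 2.2.8, replace 2019–2020 with the actual calendar years in which participants are followed. Preferably, value sick leave at the minimum daily wage of the reference year already set for drug prices (the study's final year), so that wage and drug costs share a price year. Record the change as a dated correction before the economic analysis starts.

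The cost is one sentence and one different unit price. It needs no new data, no patient contact and no change to the clinical analyses.

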#### 2.2.3. Sample Size

To calculate the sample size, we will use the data obtained in the study of Dalbosco-Salas et al. [34] because the intervention is similar to ours, and it is developed in PHC, despite being a clinical trial. To the best of our knowledge, to date there are no studies carried out with post-COVID-19 patients that evaluate a similar intervention with a clinical trial methodology. We will use the difference pre-post score of the short-form 36-item questionnaire (SF-36), the value of the possible highest standard deviation (SD), and a minimum expected difference of 19.3 points in the pre-post rating, which were all taken into account. Accepting a risk alpha of 0.05 and a power of 95% in a bilateral contrast, 70 subjects would be required. A maximum loss-to-follow-up rate of 10% has been estimated. The total sample required is 78 subjects, distributed between the two groups (control–intervention).

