Various studies, however, have revealed that early rehabilitation interventions are essential for post-COVID patients to avoid progressive deterioration before the symptoms become chronic [139]. Therefore, in addition to physical, respiratory, and cognitive interventions, this study has also included healthy lifestyle habits (adherence to the Mediterranean diet, sleep hygiene, and RHA), following the existing clinical guidelines for long COVID-19 patients in order to improve the quality of life of these patients.

This project has strengths and limitations. The strengths of this study include the design of a qualitative needs assessment and the co-creation of a community-based TR resource that can be widely used. It will provide a wealth of information on the interplay between the quality of life of people with long COVID, ongoing symptoms, and personal factors on health behaviour. Study limitations include the possible attrition of participants due to reinfections leading to health deterioration or seeking other health care resources during the course of the study. However, possible reasons for attrition and other issues will be recorded.

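### The economic analysis assumes data are missing at random but leads with complete cases; the imputation already planned should be the main analysis

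*Protocol article*

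**What the plan says.** The relevant text is in the protocol article, section 2.2.8, in the paragraph on cost-efficiency and cost-utility.

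- Assumption: "We assume that data will be missing at random (MAR").
- Analysis set: "Only patients with both cost and relevant outcome data at three and six-month follow-up will be included in the cost-efficiency and cost-utility analyses".
- Role of imputation: "Notwithstanding, sensitivity analysis imputing missing three and six-month data will test the robustness of the cost-efficiency and cost-utility results". The R package mice is named for this.
- Estimator: "ICER is defined as the ratio between incremental costs and incremental effectiveness", with the cost-utility ratio defined in the same way on QALYs. No covariate adjustment is mentioned. Adjustment for the baseline SF-36 appears only in the clinical effectiveness paragraph.

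Two other places bear on the point. Section 2.2.3 says "A maximum loss-to-follow-up rate of 10% has been estimated". Section 4 (Discussion) lists as a limitation the "possible attrition of participants due to reinfections leading to health deterioration or seeking other health care resources" during the study, and adds that reasons for attrition will be recorded.

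**The concern.** The assumption and the main method do not match. Under MAR, the chance that a value is missing may depend on things already observed, such as the baseline or three-month SF-36, symptoms or earlier costs. Imputation is built for that situation. An unadjusted comparison of complete cases needs the stronger condition that the completers in each arm are in effect a random sample of that arm. The plan puts the method its assumption supports second and the one it does not support first.

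The plan's own expectations point away from the stronger condition. Worsening health bears on the outcome, and use of other care bears on cost, so both parts of the ratio are exposed. Cost-efficiency is part of the stated objective (Abstract and Introduction), so the main ICER and ICUR would rest on the less well supported method. The plan also does not say which result stands if the two disagree.

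**Working it through.** **1. The plan's own figure.** Section 2.2.3 gives 70 participants before losses and 10% loss: 70 / (1 − 0.10) = 77.8, rounded up to 78. This reproduces. Expected losses are 0.10 × 78 ≈ 8 participants. With an equal split (the ratio is not stated) there are 78 / 2 = 39 per arm.

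**2. What the text fixes.** MAR is assumed, complete cases are the main analysis, imputation is secondary, and no adjusted economic model is given. Complete cases can be valid under MAR if missingness depends only on covariates in the analysis model. That route needs a stated model. It does not extend simply to missingness driven by the three-month score, because that score is itself measured after randomisation and may be affected by treatment.

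**3. Illustration.** All inputs below are assumed except where noted.

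- SD 22.4. The article prints no SD. This value is implied by its figures if the 70 are two arms of 35: 19.3 / [(1.960 + 1.645) × √(2/35)] = 22.4.
- SF-36 at baseline, three and six months: mean 50, pairwise correlation 0.6, treatment effect 10 points at both follow-ups.
- Cost = 1000 − 10 × (six-month SF-36 − 50) + noise with SD 300, so the true cost difference is −10 × 10 = −100 units.
- Six-month data and cost go missing with a log-odds slope of 1 per SD of the driving score, overall rate 10%, in 500,000 simulated subjects per scenario.
- Imputation: regression within arm on the baseline and three-month scores (point estimates only).

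Cost difference at 10% missing:

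| Dropout depends on | True | Complete cases | Complete cases, baseline-adjusted | Imputed |
|---|---|---|---|---|
| nothing | −100.3 | −99.9 | −99.7 | −99.9 |
| baseline score, intervention arm only | −100.0 | −114.3 | −100.9 | −100.4 |
| three-month score, intervention arm only | −101.8 | −113.7 | −106.5 | −101.8 |
| three-month score, opposite directions by arm | −99.8 | −124.8 | −110.3 | −100.3 |
| three-month score, same direction in both arms | −98.5 | −94.5 | −96.8 | −98.2 |

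In the opposite-directions case the complete-case figure moves to −147.9 (true −101.1) at 20% missing and −168.1 (true −100.9) at 30%. Imputation gives −101.2 and −100.3.

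For the SF-36 change at 10% missing:

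- Dropout on the baseline score in the intervention arm only: complete cases 9.19 against a true 10.08; baseline adjustment restores 10.09.
- Dropout on the three-month score: unadjusted complete cases are essentially unbiased, for example 10.05 against 10.02. This is a product of the equal correlations assumed.

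**4. Scale.** In this setting the cost SD is √(10² × 22.4² + 300²) = 374. With 35 completers per arm the standard error of the difference is 374 × √(2/35) ≈ 89. The shifts at 10% missing in the three arm-dependent rows are 11.9 to 25.0 units, or about 0.13 to 0.28 of a standard error.

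**The case against.** The strongest reply is that the imputed result will be produced anyway, so only the label of main analysis is in dispute, and a condensed article need not say whether incremental costs and effects come from an adjusted model. Both points soften the concern. They do not remove it: the main ratios still rest on complete cases, and in the illustration baseline adjustment left the cost difference at −110.3 against −99.8 when dropout followed the three-month score in opposite directions.

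A second reply is that dropout after a reinfection or a change of care that follows the last observation may not be MAR at all, so imputation under MAR would not remove that bias either. This stands, and the fix needs a departure-from-MAR check. The imputation in the illustration also succeeds partly because its model matches how the data were generated.

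Several stronger readings are tempting but not supported:

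- *About 19% would be excluded* (1 − 0.9² = 0.19). This applies 10% independently at each visit. The plan's 10% is a maximum overall loss, and a person lost by three months is usually also missing at six.
- *A participant missing one visit is dropped entirely.* Requiring both visits is the natural reading. The sentence can also be read as requiring cost and outcome together at each visit, with separate three- and six-month analyses.
- *The randomised comparison is broken.* Bias may be small, or largely cancel if dropout is similar in the two arms.
- *The clinical and economic analyses use different populations.* The article does not say how the repeated-measures regression treats missing visits, so this is inference.

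**Conclusion.** The mismatch is in the text and is certain: MAR is assumed, complete cases lead, and imputation is secondary. It concerns the economic analyses only. The size and direction of any bias cannot be derived from the documents. Under the assumed inputs, at 10% missing, it is roughly 12 to 25% of the true cost difference when dropout differs by arm, about 4% when it does not, and well inside sampling error for a trial of this size. It grows with the missing rate, and more participants are excluded if data at both visits are required. This is a recommended change rather than a fatal flaw. No sample size, alpha or power figure is affected.

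**What to change.** Swap the roles in section 2.2.8:

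- **Main economic analysis:** all randomised participants, in the arm to which they were allocated, with missing three- and six-month costs and outcomes multiply imputed using mice.
- **Imputation model:** parsimonious, including arm (imputing separately by arm only if that proves stable), baseline and interim SF-36, symptoms and costs. The six-week call on reinfection and treatment changes (section 2.2.7) could supply an auxiliary predictor.
- **Uncertainty:** carry imputation uncertainty into the ICER and ICUR, by Rubin's rules on incremental costs and effects or by bootstrap combined with imputation.
- **Sensitivity analyses:** complete cases, and one simple departure-from-MAR scenario in which imputed values are shifted to be worse or costlier, using the recorded reasons for attrition.
- **Wording:** say whether complete-case status requires both visits or is judged visit by visit.

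The cost is plan wording and some extra analysis, in software already named. The downside is possible instability of the imputation model with about 39 participants per arm and skewed costs, which is why it must stay small. The article reports 60 participants randomised and recruitment still being completed, so the change can be fixed before the economic data are analysed.
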